#### 2.2.2. Adherence Assessment

Participants will visit the laboratory weekly to receive new supplements and related information, which will be registered on case report formats. Treatment adherence will be assessed by counting the remaining capsules when the participants return to the laboratory. Participants will be asked to report as soon as an adverse effect occurs to analyze the possibility of suspending supplementation.

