### 2.2. Interventions

The clinical trial consists of two interventions: (1) supplementation with *S. maxima* (5 g/day) or placebo (5 g/day of a low-calorie saccharine), and (2) an exercise program, during a period of 24 weeks in a randomized, double-blind, counterbalanced, crossover, controlled trial with a 2 × 2 factorial design. Presentation of both supplements will be powder encapsulated in dark capsules of 0.5 g to present the same organoleptic attributes and mask their individual characteristics.

Inclusion in the exercise program intervention will be decided by each participant, who will be randomly assigned to one of the two possible nutritional interventions (*S. maxima* or placebo) categorized into four treatments: an exercise program plus *S. maxima* intake; exercise with placebo administration; *S. maxima* intake without exercise, or placebo supplementation without exercise program (Control). To assess compliance to the supplement intake, a crossover will be conducted for the supplementation interventions.

The first period of treatment will be carried out for 12 weeks, followed by a four-week wash-out period to avoid any possible delayed effect of *S. maxima* in the organism. Finally, a further 12 weeks of treatment for the second intervention groups (Figure 1).

Due to absence of data related to wash-out and treatment periods length, we considered 4 and 12 weeks, respectively, as stated by a systematic review of clinical trials that used spirulina as treatment [22].

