#### 2.2.1. Exercise Program

Participants in the exercise program groups will exercise five days a week. The physical activity program will be conducted in accordance with the American College of Sports Medicine recommendations [23] and will consist of Monday to Friday chair exercises performed during 24 weeks.

The approximate exercise duration will be of 40–50 min. Each exercise session has an initial or warm-up phase of 5–10 min (joint movement exercises to increase body temperature starting with movements of head, upper extremities trunk, hip, and, lower extremities); a main physical conditioning phase of 25–30 min that will consist of developing a personalized circuit of strength exercises of the main muscle groups (arms, shoulder, chest, back, and legs) at moderate intensity (between 3.0 and 6.0 metabolic equivalents of task (METs)) using rating of perceived exertion scale and the Talk Test; finally, a cool-down or relaxation phase of 5–10 min. To define the individual exercise intensities in the main physical conditioning phase, participants will have a training of 3 to 5 days before the beginning of the clinical trial to learn how to use the rating of perceived exertion scale and the Talk Test as markers of exercise training intensity.

Trained personnel will assist older adults to perform the exercise program, including articular flexibility, postural exercises, and proprioception exercises. These activities will be selected according to the individual deterioration and joint stiffness that the participants could present. Researchers are trained in cardiopulmonary resuscitation and the laboratory has the necessary tools and communication channels to carry out emergency procedures if a participant presents any side effect of exercise.

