### 2.7. Ethics

Participants will be informed of the study rationale as well as all procedures. Their inclusion will be formalized by signing an informed consent (Supplementary File 3), being anonymity and confidentiality carefully enforced, and all participants data will be stored during five years after the study completion. The protocol and procedures have been approved by the Autonomous University of Baja California (UABC) bioethics committee (Supplementary File 4). One UABC scientific committee member and one UABC bioethics committee member will have always access to the interim results and can decide to terminate the trial according the adverse events or unintended effects that could be presented during trial conduct. The clinical trial has been registered prospectively at ClinicalTrials.gov database (Date of approval: 10 December 2020; Identification number: NCT04658875), moreover, the World Medical Association’s Declaration of Helsinki guidelines [36] will be followed.

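### Adverse effects are collected only through a participant-initiated report tied to suspending the supplement, and no recording step is stated for side effects of exercise, so harms information may be incomplete and unevenly detected

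*Protocol article*

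**What the plan says.** Section 2.2.2 (Adherence Assessment) of the protocol article holds the one stated rule for collecting harms: "Participants will be asked to report as soon as an adverse effect occurs to analyze the possibility of suspending supplementation". The same section sets the contact schedule for all groups: "Participants will visit the laboratory weekly to receive new supplements and related information, which will be registered on case report formats". It does not say that an adverse-event question is part of that visit.

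Section 2.2.1 (Exercise Program) adds contact for one part of the sample: "Participants in the exercise program groups will exercise five days a week". Staff are present: "Trained personnel will assist older adults to perform the exercise program, including articular flexibility, postural exercises, and proprioception exercises". The section expects that exercise may cause harm, since researchers are trained and the laboratory is equipped "to carry out emergency procedures if a participant presents any side effect of exercise". That describes a response to an event. It does not say that the event is written down, or where.

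Section 2.7 (Ethics) gives two committee members standing access to interim results and says that they "can decide to terminate the trial according the adverse events or unintended effects that could be presented during trial conduct". It does not say how events reach them.

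On who exercises, section 2.2 says: "Inclusion in the exercise program intervention will be decided by each participant". Only the supplement is randomised.

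**The concern.** The trial tests two interventions in sedentary people aged 60 or over. The stated route for harms is passive, and its stated purpose concerns only one of the two. A participant who falls at home, or has joint pain some days after a session, may not think of it as an adverse effect, or may see no reason to report it when the report is framed as a question about the capsules. If staff handle an event during a session, nothing stated carries it into the trial record.

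Two things are at stake. The first is completeness: the power to terminate in section 2.7 covers adverse events of any origin, which is wider than the purpose given in section 2.2.2. The second is comparability: exercisers are seen by staff far more often than non-exercisers, so a tally of events by exercise group could reflect opportunity to notice events as well as their occurrence.

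**Working it through.** The article gives no figure for harms (no expected event rate and no detection rate), so there is no figure of the plan to reproduce. The sample size of at least 52 does not depend on this point.

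**Step 1. What each section covers.**

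| Section | Who acts | Scope | Recording stated? |
|---|---|---|---|
| 2.2.2 | Participant reports | An adverse effect, origin not restricted; stated use is suspending the supplement | Not for the report itself; visits use case report formats |
| 2.2.1 | Staff respond | Side effects of exercise | No |
| 2.7 | Two committee members decide on termination | Adverse events of any origin | Source of their information not stated |

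The decision in 2.7 has the widest scope. The only collection rule, in 2.2.2, is passive and has the narrowest stated purpose. Nothing in the text connects 2.2.1 to either.

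**Step 2. Staff contacts per 12-week period.** Inputs: weekly visits for all (2.2.2), five sessions a week for exercisers (2.2.1), and attendance below 80% as an exclusion/elimination criterion (Table 1).

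- Non-exercisers: 1 × 12 = 12 visits.
- Exercisers, sessions: 5 × 12 = 60; at 80% attendance, 0.80 × 60 = 48.
- Exercisers, total if visits and sessions are separate: 60 + 12 = 72; at 80% attendance, 48 + 12 = 60.
- Ratio: 72/12 = 6; at 80% attendance, 60/12 = 5.

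The article does not say whether the weekly visit falls on a session day. If each visit coincides with an attended session, the counts are 60 or 48 contacts against 12, a ratio of 5 or 4.

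**Step 3. What unequal detection could do (illustration only).** Let observed risk = true risk × probability of capture, with the same true risk in both groups. The apparent risk ratio is then capture in exercisers divided by capture in non-exercisers. All capture rates here are assumptions.

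| Capture, exercisers | Capture, non-exercisers | Apparent risk ratio |
|---|---|---|
| 0.5 | 0.5 | 0.5/0.5 = 1.0 |
| 0.7 | 0.5 | 0.7/0.5 = 1.4 |
| 0.9 | 0.5 | 0.9/0.5 = 1.8 |
| 0.9 | 0.8 | 0.9/0.8 = 1.13 |
| 0.9 | 0.4 | 0.9/0.4 = 2.25 |

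With an assumed true risk of 20% and an assumed 26 participants in each exercise stratum, 26 × 0.20 = 5.2 true events per stratum. Capture of 0.5 shows 2.6 of them, 0.7 shows 3.6 and 0.9 shows 4.7. The first row matters as much as the others: if reporting is equal, there is no distortion between groups, only loss of events.

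**Step 4. The supplement contrast.** *S. maxima* and placebo are randomised, blinded and crossed over within each exercise choice, with the same contact schedule. Capture is then expected to be equal on both sides. Missed events lower both counts, but contact frequency does not shift their ratio.

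**The case against.** The strongest reply is that this is a condensed article. The adverse-event form, grading and scheduled enquiry may be in the full protocol or the case report formats, which are not shown. That stands as far as it goes: the absence of a form or of grading is not the point here. But section 2.2.2 is not merely silent. It states a method, and that method is passive and tied to one intervention.

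A reader might also draw stronger conclusions that the document does not support:

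- *Only harms of the supplement are collected.* The sentence does not restrict the origin of the effect. An exercise injury could be reported by the same route; only the stated purpose is limited to supplementation.
- *Exercise harms are ignored.* Section 2.2.1 provides assisting staff and an emergency response. What is missing is a stated recording step.
- *Events are under-counted and detection differs.* These are foreseeable risks. With no event or capture rates, neither can be shown.
- *The committee members rely on this stream alone.* Section 2.7 does not say what information they receive beyond access to interim results.

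There is a further objection of logic. If capture is by self-report only, more staff contact is not itself a route to more recorded events. If staff at sessions do pick events up, exercise harms have a route in practice. Both cannot hold at once, but either leaves a weakness. In the first case, events seen by staff are lost unless the participant volunteers them. In the second, one group has a source of events that the other lacks.

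Finally, the article plans no between-group harms analysis, and the exercise contrast is self-selected, which the limitations section declares. Both are correct and they limit the weight of the point. They do not touch the completeness of the information for the termination decision, and confounding by choice is no reason to accept an avoidable detection difference as well.

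**Conclusion.** The point holds in a limited form. The only stated collection method for harms is a participant-initiated report, linked to suspending the supplement, and no recording step is stated for side effects of exercise. Events may therefore be missed, and what is available for the termination decision may be incomplete.

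A harms comparison by exercise group, if one were made, would be open to unequal detection. The contact difference is 5 to 6 fold if visits and sessions are separate, and 4 to 5 fold if they coincide. The effect on any risk ratio cannot be computed. The illustrative 1.0 to 2.25 rests wholly on assumed capture rates and says nothing about what will happen in this trial. The *S. maxima* versus placebo contrast is not biased by contact frequency. No planned estimate, test or sample size changes.

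This is a weak choice of method that a better one can replace cheaply. It is not an error that invalidates the design.

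**What to change.** In section 2.2.2, keep the immediate self-report and add text to this effect:

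> At every weekly visit, in every group, staff ask the same open, non-leading question about any health problem since the last visit. Every event is entered on the case report form regardless of presumed cause, whether supplement, exercise or neither. Events observed by staff during exercise sessions are recorded separately. Any between-group summary of harms uses the answers to the weekly question only. The cumulative list of all events is available to the two committee members named in section 2.7.

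Add a cross-reference in section 2.2.1, so that an event handled at a session is also recorded.

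The weekly question gives all groups the same scheduled opportunity to report. It cannot guarantee equal willingness to report, and the exercise comparison stays non-randomised.

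The cost is a wording change, space on the existing form and a few minutes at visits that already include dietary recalls (2.3.2) and mental health instruments (2.3.5). More minor events will be recorded. No rule for stopping the supplement or the exercise is proposed.

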### 2.3. Outcome Measures

Primary outcome will be the change in body composition (body fat percentage, muscle mass percentage, and BMI) of sedentary overweight older adults. We will include as secondary endpoints the energy intake (total calories, proteins, carbohydrates, fat, and micronutrients consumption), genetic markers, and the changes in blood lipid profile (TC, HDL-C, LDL-C, and TG), physical function (grip strength and functional physical condition), sleep-wake patterns, mental health (anxiety, depression, and cognitive performance), inflammatory markers (IL-6 and TNF-α) of sedentary elderly with excess body mass. Health organizations around the world recommend studies focused on improving these response variables [24]. An overview of all variables included in the SIE trial is shown in Table 2.

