Therefore, we hypothesize that the administration of *S. maxima* alone or together with an exercise plan will decrease the body fat percentage and blood lipids while increasing physical function in sedentary elderly patients with excessive body mass in a randomized, double-blind, counterbalanced, crossover, controlled trial. The main objective of our research is to evaluate the independent and synergistic effect of 12 weeks of *S. maxima* intake (compared to placebo), with or without an exercise program on the body composition (body fat percentage, muscle mass percentage, and body mass index (BMI)) in sedentary older adults with excessive body mass. The secondary objective is to test the effects of both interventions in the blood lipid profile, energy intake, physical function, sleep wake patterns, mental health, and inflammation, as well as to analyze the influence of the genetic background in all outcomes in older adults with excessive body mass.

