#### 2.3.1. Body Composition

Body mass will be measured in participants with light clothes and barefoot using an electronic balance and standing height with a clinical stadiometer. Body composition (body fat percentage, muscle mass percentage and BMI) will be measured by three techniques: air displacement plethysmography (BodPod, COSMED, Rome, Italy); electric bioimpedance (InBody770, BIOSPACE, Tokyo, Japan); and anthropometry following the standardized protocols of the International Society for the Advancement of Kinanthropometry (ISAK) [25]. The anthropometric variables to include are the ones of the restricted profile (height, body mass, skinfolds (tricipital, subscapular, bicipital, suprailiac, supraspinal, abdominal, anterior thigh, and medial calf)), girths (relaxed arm, flexed arm, waist, hip, and calf) and skeletal breadths (humerus and femur). The measurements’ margin of error will be <2% for skinfolds and <1% for girths and skeletal breadths. Anthropometric dimensions will be measured twice (thrice when measurements are greater than the margin of error) and recorded as a mean. Researchers are certified as ISAK anthropometrists (Supplementary File 2) and are experienced in handling equipment and procedures. Phase angle (50 kHz) will be obtained from the electric bioimpedance analysis.

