### 2.6. Statistical Methods

Normality and homoscedasticity of variables will be screened by the Shapiro–Wilk and the Levene tests, for each group. The analysis of statistical differences among treatments and time, univariate repeated measures ANOVA with two within-participants (initial and final values), and four inter-participants (treatments) factors will be used. Moreover, basal and post-treatment values will be contrasted by paired *t*-tests. Delta values will be analyzed by one-way ANOVA and Tukey Post-hoc tests (normal distribution and equal variances) and Kruskal-Wallis H and Dunn’s Post-hoc test (non-parametric distribution and unequal variances), with Bonferroni setting for multiple comparisons. Spearman correlations will be run to evaluate the associations among variables. Eventual gen-diet and gen-exercise interactions concerning anthropometric and metabolic outcomes will be assessed by univariate regression analyses. Statistically significance will be set at a *p*-value of 0.05. All statistical analyses will be completed using IBM SPSS package version 23 (SPSS Inc, IBM Company, Chicago, IL, USA) and STATA software (StataCorp, College Station, TX, USA).

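### The primary outcome is three unranked variables read by three techniques at 0.05, with no rule across them, so the primary error rate exceeds 5%

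*Protocol article*

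**What the plan says.** All references are to the protocol article.

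- **Primary endpoint.** Section 2.3: "Primary outcome will be the change in body composition (body fat percentage, muscle mass percentage, and BMI". The main objective in section 1 lists the same set, "on the body composition (body fat percentage, muscle mass percentage, and body mass index (BMI", and Table 2 repeats it. No variable is placed first.
- **Measurement.** Section 2.3.1: "Body composition (body fat percentage, muscle mass percentage and BMI) will be measured by three techniques". These are air displacement plethysmography, bioimpedance and anthropometry. The section does not say which one supplies the primary value.
- **Level.** Section 2.6: "Statistically significance will be set at a *p*-value of 0.05". No division of this level among outcomes is described.
- **Adjustment.** The only one is "with Bonferroni setting for multiple comparisons". It closes the sentence on change scores, directly after the Tukey and Dunn post-hoc tests.
- **Analyses.** Section 2.6 lists a repeated measures ANOVA, paired t-tests on before and after values, and one-way ANOVA or Kruskal-Wallis tests on change scores. None is named as primary.
- **Sample size.** Section 2.4 uses significance 0.05 and power 0.85, giving at least 52 participants. It names no outcome variable.
- **Hypothesis.** The final paragraph of section 1 predicts a fall in body fat percentage. It does not mention muscle mass percentage or BMI.

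**The concern.** A primary endpoint made of several variables needs a rule that links them. One variable may lead, all may have to succeed, or the level may be shared among them. The article gives three variables and one undivided level, with no such rule. Each variable is then a separate primary test at 0.05, and the chance that at least one is significant by luck is above 5%.

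The three techniques add a second layer. Plethysmography, bioimpedance and skinfolds can disagree in the same person. If they do, nothing in the article says which result is the trial's primary result, and that choice could be made after the data are seen. What is at stake is how the main conclusion can be read, and this cannot be repaired credibly after unblinding.

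**Working it through.** **1. The plan's own figure.** The article states no family-wise error rate. Its one related figure is the sample size of at least 52. That cannot be reproduced, because section 2.4 gives no effect size, standard deviation, correlation, test or variable. It can be said only that the calculation used an undivided 0.05.

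**2. Inputs.** Three primary variables (sections 1 and 2.3), three techniques (2.3.1), 0.05 per test (2.6). Two-sided tests are assumed, as the article does not state sidedness.

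**3. Scope of the Bonferroni clause.** It stands in the sentence that compares change scores among treatments and follows two post-hoc procedures for treatment pairs. It therefore adjusts comparisons within one outcome. Nothing extends it across outcomes or techniques.

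**4. Three independent tests.** Chance of at least one false positive = 1 − (1 − 0.05)^3 = 1 − 0.8574 = 0.1426, or 14.3%.

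**5. Correlated tests.** The variables are related, so 14.3% is an upper limit for three tests. The article gives no correlations, so a range is assumed. Each case simulates 400,000 sets of equally correlated two-sided z tests. The sign of a correlation does not matter for two-sided tests.

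| Readings tested | Independent | r = 0.5 | r = 0.7 | r = 0.9 |
|---|---|---|---|---|
| 3 | 14.3% | 12.6% | 10.9% | 8.3% |
| 5 | 22.6% | 18.3% | 14.9% | 10.2% |
| 7 | 30.2% | 22.9% | 17.8% | 11.4% |

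The independent column for five and seven is 1 − 0.95^5 = 0.2262 and 1 − 0.95^7 = 0.3017.

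**6. Where five and seven come from.** BMI needs only weight and height, so it counts once. Body fat by three techniques, muscle by one and BMI gives 3 + 1 + 1 = 5. With muscle by all three techniques it is 3 + 3 + 1 = 7. These counts apply only if each technique is tested separately.

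**7. Cost of keeping all three as primary (illustration on assumed inputs).** Take the group-by-time interaction with 4 groups, 2 times, effect size f = 0.25 and correlation 0.5 between repeated measures. The noncentrality is f² × N × m / (1 − ρ) = 0.0625 × 52 × 2 / 0.5 = 13, on 3 and 48 degrees of freedom.

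- At 0.05: power with 52 participants is 0.84, and 56 in balanced groups reach 0.85.
- At 0.05/3 = 0.0167: power with 52 is 0.70, and about 68 reach 0.85.

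Holm is never less powerful than Bonferroni, so 0.70 is a floor for each variable under Holm on these inputs.

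**The case against.** **The plan does not say it will claim success on any one variable.** This is correct. A reader might infer that the trial is free to declare success on whichever variable is significant, but no section says so. A rule requiring all three to succeed would not inflate the error at all. What stands is that the article states neither rule, and that running its three tests at its stated level gives a chance above 5% of at least one false significant primary result.

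**An unseen analysis plan may set the order.** A full protocol or analysis plan could rank the variables and choose the technique, and an article may leave such detail to it. But the three-part primary definition and the single 0.05 level are themselves stated here, so the point does not rest only on missing detail.

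**The hypothesis favours body fat percentage.** It does, and the conclusions also call excess body fat the main risk factor. That is a good reason to choose this variable, but it is not a ranking: sections 1, 2.3 and Table 2 still list three.

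**Bonferroni is specified.** Its scope is not expressly limited, so a wider meaning cannot be excluded. Its position makes the post-hoc reading much the more natural.

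**The larger figures overstate.** In part they do. Seven readings is a high count, the correlations are assumed, and techniques that measure the same quantity will be strongly related. At 0.9 the figures fall to 8.3% (three) and 11.4% (seven), still above 5%.

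**Muscle as a percentage.** A reader might infer that this variable is itself an error, since the percentage can rise through fat loss alone. The article does not say that a rise will be reported as muscle gain, and body fat percentage is a ratio too. This is a matter of interpretation.

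**Conclusion.** The point holds in this form: an unranked three-variable primary outcome, three techniques with none named as primary, one 0.05 level and no rule across them. The firm figure is for the three variables alone: 14.3% if independent, and about 8% to 13% at assumed correlations of 0.9 to 0.5. Separate testing by technique raises it, to at most 22.6% to 30.2% for five to seven readings.

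These figures assume no true effect on any variable and two-sided tests. The correlated values come from z tests, not from the omnibus F tests that section 2.6 also lists. The several analyses in 2.6 add further choice that is not counted here. The documents do not show an intention to select the favourable result; they fail to rule it out.

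**What to change.** **Section 2.3.** Name change in body fat percentage as the single primary variable, from one prespecified technique. Air displacement plethysmography is one possibility; the choice is a judgement that the article does not settle. Treat the other techniques as sensitivity readings.

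**Section 2.6.** Name the randomised *S. maxima* versus placebo contrast as the primary test at two-sided 0.05. Test muscle mass percentage and BMI as key secondary outcomes in fixed order or by Holm. Keep the supplement-by-exercise (synergy) question as a prespecified secondary analysis, because participants choose exercise themselves (section 2.2 and Strengths and Limitations).

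**Cost.** A short text change in each section, no new measurement, and no increase in sample size on account of multiplicity. The real price is that muscle mass percentage and BMI lose primary status and that synergy, part of the stated main objective, is no longer the primary test.

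**Alternative.** Keep all three variables as primary under Holm, still with one technique named, and recompute the sample size. This loses some power, as illustrated in the working.

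Reporting muscle mass in kilograms beside the percentage is an optional aid to interpretation.
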